## SPECIFIC HYPOTHESES AND AIMS

### Part 1: Effect of VLED versus conventional diet on parameters that affect body composition

**Hypothesis:** Whilst the ketogenic state induced by VLED abates some of the adaptive responses that can oppose weight loss, promote regain and impair body composition, VLED will nonetheless induce stronger overall adaptive responses to weight loss than conventional diet.

**Aim:** To compare the effects of VLED versus conventional diet in obese adults on appetite, physical activity, metabolic rate, neuroendocrine status, circulating gut hormone concentrations, markers of bone turnover and sympathetic reactivity up to 12 months after commencement of each intervention. Groups will be matched by the amount of weight or fat lost (at differing time points) as well as by duration of intervention (at different levels of weight or fat lost). We will also compare the magnitude of these parameters before and 1 week after transition from the ketogenic VLED to the non-ketogenic conventional diet, to determine the effect of ketosis on these responses.

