### Part 2: Effect of VLED versus conventional diet on body composition

**Hypothesis:** While VLED will promote greater initial weight and fat losses than conventional diet, it may also promote greater losses of lean body mass, muscle diameter, muscle strength and bone density that may not be recovered, and a greater propensity for fat regain, particularly abdominally.

**Aim:** To compare the effects of VLED versus conventional diet in obese adults on body weight, waist and hip circumference, adiposity (including central adiposity and hepatic fat), lean body mass, muscle diameter, muscle strength and bone density for 36 months after the start of interventions.

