**Time points and matching between groups.** At 0, 0.25, 1, 3, 6 and 12 months after commencement of each diet, the adaptive responses to weight loss summarized in the above figure (top box) will be assessed. The necessity of measuring these parameters at 6 different time points is twofold. Firstly, as the magnitude of adaptive responses to weight loss increases with the amount of weight lost, multiple time points will enable us to compare subjects on the VLED and conventional diet after a similar degree of weight or fat loss. For the purposes of matching and standardization of results, at each of these time points we will also measure weight, waist circumference, as well as fat mass and fat free mass using the 4-compartment model (without DXA) as described below and as previously published by [name]. Past experience from thousands of patients shows that weight losses after 0.25, 1 and 3 months on the VLED are similar to those induced by 1, 3 and 6-12 months on the conventional diet, respectively. In addition to matching for the degree of weight or fat loss, groups will also be compared at the same time points. A second reason for measuring these parameters at 6 time points is to determine the time of onset of various adaptive responses to weight loss, which will then be used to improve obesity interventions. For instance, we know that 2-3 months on a VLED induces strong adaptive responses that can promote weight regain and adverse body compositional changes. However, it is not known whether these responses are present for the entire duration of the VLED. If, for example, we discover that VLED (or conventional diet) induces changes such as increases in appetite and circulating cortisol levels or decreases in metabolic rate or serum IGF-1 that are seen only at the 3-month but not at the 1-month time point, then a future strategy might be to apply the intervention in intermittent bursts of less than 1 month, thereby attenuating the adaptive responses and their potentially deleterious effects on body composition.

**Effect of ketosis on parameters that affect body composition.** Participants in the VLED group will participate in this additional study. Following measurement of the adaptive responses to

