weight loss at 3 months (at which point all participants will still be on the VLED, which results in ketosis due to its low carbohydrate and kilojoule content), participants will switch to a maintenance diet for 1 week followed by re-measurement at  $t = 3.25$  months. Fasting serum concentrations of ketones such as  $\beta$ -hydroxybutyrate will also be determined before and after this transition.

**Appetite.** Participants will be provided with a fixed (200 kcal) liquid meal (Optifast®, Nestlé Nutritionals, Vevey, Switzerland) at 9:00 am. Subjective measures of motivation to eat will be measured immediately before, after and at 1, 2 and 3 hours thereafter using the Electronic Appetite Rating System as described by [name].

**Physical activity.** Intensity and duration of daily physical activity will be measured using the Actigraph triaxial accelerometer worn on the waistband or on a belt. Accelerometry data will be collected during waking hours in the 7 days preceding each time point as previously described by [name]. Descriptive data will also be recorded in an activity diary, which will enable understanding of reasons for taking off the accelerometer (e.g. to swim or to sleep). Although all subjects will have the same standardized prescription to encourage physical activity, accelerometry and activity diary data combined with information from questionnaires (below) will provide insight as to possible effects of VLED or conventional diet on time spent exercising, in non-exercise activities or inactivity, and subjective measures of sleepiness.

**Resting metabolic rate** will be measured in the fasted state via indirect calorimetry using the TrueOne 2400 (Parvo Medics, Sandy, UT, USA) ventilated hood. Respired gases will be measured continuously for 30-min.  $VO_2$  and  $VCO_2$  will be converted to resting metabolic rate using the modified Weir equation as previously published by [name].

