**Sympathetic reactivity.** Deep inspiration induces vasoconstriction in skin capillaries via sympathetic activation, and dynamic weight loss has been shown to inhibit this response, possibly by the same hypothalamic alterations that induce the various adaptive responses to weight loss. Sympathetic reactivity will thus be assessed by inspiration-induced vasoconstriction, as determined by laser Doppler fluximetry (MoorVMS-LDF® Laser Doppler Blood Flow Monitor, Moor, England) as previously published. Because reduced sympathetic reactivity determined by this method predicts poor weight loss after bariatric surgery, and because this parameter is simple to measure and non-invasive, it may serve as a predictor of poor outcomes for weight loss or body composition in response to VLED or conventional diet. Such a measure could then be used in clinical practice to help identify individuals in likely need of more intensive support.

**Questionnaires.** Participants will complete validated instruments to assess quality of life (SF-36), depression symptoms (CES Depression Scale), Health Locus of Control (Multi-dimensional Health Locus of Control Questionnaire), sleep quality (Epworth Sleepiness Scale) & physical activity.

**Database maintenance and data analysis.** We have already developed a model database for use in our clinical research facility, and in collaboration with the NHMRC Clinical Trials Unit we are developing a database that can be used nationally. Database maintenance and data entry will be performed by [name] and will be directly overseen by Associate [name]. All data analyses will be performed using the SPSS statistical software package version 17.0 (SPSS Inc, Chicago, IL, USA). Repeated measures ANCOVA will be used for comparisons between all subjects on the VLED and the conventional diet, adjusting for confounding variables such as the amount of weight or fat lost or the length of time on the diet. Paired T-tests will be used to determine whether switching from the ketogenic VLED to the non-ketogenic maintenance diet alters the magnitude of any of the adaptive responses to weight loss.

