**Outcomes Part 1:** This study will show for the first time whether VLED induces stronger adaptive responses to weight loss than conventional diet independent of the amount of weight or fat lost, and – by analysis with results in Part 2 – whether the magnitude of any of the adaptive responses predict outcomes for body composition and muscle diameter or strength. If so, then those adaptations could become targets for interventions to enhance weight loss and body composition in response to VLED or conventional diet. This work will also demonstrate whether ketones attenuate any of the adaptive responses to weight loss during VLED. If so, and if the magnitude of any adaptive responses predict outcomes for weight loss and body composition, then clinical interventions to ensure that patients on VLEDs maintain high circulating concentrations of ketones (e.g. by emphasizing the importance of compliance with the diet) could improve the effectiveness of VLEDs for the long-term management of overweight and obesity. An additional benefit of measuring multiple aspects of the adaptive response to weight loss at various time points is that it will enable subsequent improvements to both dietary interventions (e.g. by intermittent application of energy restriction), as well as early clinical identification of responders versus non-responders on both diets, thereby aiding the clinical management of obesity by targeting individuals with the greatest support needs.

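### For resting metabolic rate, matching or adjusting on weight lost or fat lost alone leaves fat-free mass free to differ between diets, so plain lean loss could be read as a stronger adaptive response

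*Supplement*

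**What the plan says.** All references are to the Supplement. The final protocol is only linked there (section 1.2), so section 1.1 is the latest Part 1 text available.

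- **Outcome list.** The Part 1 aim compares the diets "on appetite, physical activity, metabolic rate, neuroendocrine status, circulating gut hormone concentrations", among other responses.
- **Measurement.** Gas exchange "will be converted to resting metabolic rate using the modified Weir equation". This gives an absolute rate; no scaling to body composition is stated.
- **Matching.** The Part 1 aim says: "Groups will be matched by the amount of weight or fat lost (at differing time points", and adds comparisons at equal duration. The paragraph on time points repeats the same basis.
- **Model.** Part 1, Database maintenance and data analysis, specifies repeated measures ANCOVA, "adjusting for confounding variables such as the amount of weight or fat lost or the length of time on the diet".
- **Claim.** Outcomes Part 1 says the study will show "whether VLED induces stronger adaptive responses to weight loss than conventional diet independent of the amount of weight or fat lost".
- **Data available.** At each Part 1 time point the trial measures weight and waist "as well as fat mass and fat free mass using the 4-compartment model", for matching and for standardizing results.
- **Lean mass.** The Part 2 hypothesis is that VLED will give greater initial weight and fat loss and that "it may also promote greater losses of lean body mass, muscle diameter, muscle strength and bone density". The Part 2 measurement section also allows that the diets may affect fat-free mass differently.

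The final analysis plan (section 2.2) has lean mass at 12 months as the primary outcome and adds weight at each time point in a secondary model. It does not mention metabolic rate. None of the changes listed in sections 1.3 and 2.3 touches this point.

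**The concern.** Resting metabolic rate depends on how much tissue there is, and on lean tissue more than fat. An adaptive fall is one that exceeds what the lost tissue explains. To isolate it, the comparison has to hold both lean and fat tissue constant.

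The plan names weight lost or fat lost, as alternatives. Weight is fat plus fat-free mass, so fixing only one of weight and fat leaves fat-free mass free to differ between the diets. A lean gap at equal loss would then show as a lower metabolic rate on VLED with no adaptation at all, in the direction of the Part 1 hypothesis.

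A trial whose primary outcome is a between-diet difference in lean mass should not leave this open. Outcomes Part 1 also proposes to use adaptive responses as predictors of body composition and as targets for intervention. A fall in metabolic rate that only reflects lean loss would mislead in both uses.

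**Working it through.** **The plan's own figure.** The only sample-size figure tied to metabolic rate is in the Sample size section: an effect size above 1.1 in the first 3 months, with 5 per group for 90% power. At exactly 1.1 the two-sided normal formula gives 18 per group; 5 per group needs an effect size of about 2.05 (normal) or 2.35 (t). Since 1.1 is given as a lower bound, this is not a contradiction. No matching is mentioned there, and nothing below depends on it.

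**Set-up.** Let L be lean loss, F fat loss and W = L + F weight loss. Suppose there is no adaptive difference between the diets, so that

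change in metabolic rate = −bL × L − bF × F + noise.

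**Inputs.**

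- From the documents: 40 women per arm (50 less 20% attrition).
- Assumed, because the documents give none: bL = 10, 20 or 30 kcal/day per kg lean; bF = 4.5 kcal/day per kg fat; residual SD 80 kcal/day; W with mean 12 kg and SD 4 kg; L = 0.22 × W plus scatter of SD 1.2 kg; and an extra lean loss g on VLED at equal weight lost. Body composition is taken as measured without error.

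**Bias when adjusting for weight lost.** At equal W, g kg more lean loss means g kg less fat loss, so the two partly offset:

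bias = −(bL − bF) × g.

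For g = 1 kg: −(10 − 4.5) = −5.5 to −(30 − 4.5) = −25.5 kcal/day.

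**Bias when adjusting for fat lost.** Within an arm, the regression slope of L on F is (0.22 × 0.78 × 16 − 1.44) / (0.78² × 16 + 1.44) = 1.306 / 11.174 = 0.117. A gap of g at equal weight lost is therefore a gap of 1.117 × g at equal fat lost:

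bias = −bL × 1.117 × g.

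For g = 1 kg: −11.2 to −33.5 kcal/day.

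**Simulation** (2,000 trials per case, two-sided 5% test):

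| Extra lean loss g | Adjusted for weight lost: bias; false positives | Adjusted for fat lost: bias; false positives | Adjusted for lean and fat lost: bias; false positives |
|---|---|---|---|
| 0 kg | within 1 kcal/day; about 5% | within 1 kcal/day; 5% to 6% | within 1 kcal/day; about 5% |
| 1 kg | −6 to −25 kcal/day; 7% to 25% | −11 to −33 kcal/day; 9% to 36% | within 1 kcal/day; 4.5% to 6.4% |

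The ranges run over bL = 10 to 30. The simulated biases agree with the formulas. The joint model is correctly specified here, so its true rate is 5% and the 4.5% to 6.4% spread is simulation error. Entering weight lost and fat lost together gives the same result as lean and fat, because W = L + F. The difficulty is the word *or* between the two named variables.

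**The case against.** The strongest reply is that the plan has not decided to ignore lean mass. The covariates in "adjusting for confounding variables such as the amount of weight or fat lost or the length of time on the diet" are examples, not a closed list. Fat-free mass is measured at every Part 1 visit, and standardizing results is a stated purpose; because it is not a matching variable, using it to standardize outcomes is a natural reading. One of the studies cited for the method concerns lean-mass distribution and resting metabolic rate after weight loss. The final protocol is not shown, and the final analysis plan covers lean mass, bone density and body composition, so its silence on metabolic rate is weak evidence.

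This stands to a degree. A reader might infer that lean loss *will* be reported as adaptation; the documents do not support that. They show an unspecified model. But the matching statement, the named covariates and the promised conclusion all rest on weight or fat, and no rule says how fat-free mass enters. The adjustment could therefore be chosen after the results are seen.

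A reader might also infer that the trial expects more lean loss on VLED at the same loss. It does not say so. The Part 2 hypothesis says only that VLED may cost more lean mass, beside greater initial weight and fat loss, and does not condition on equal loss.

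Finally, the 2.7 kg planning difference in lean mass (50.3 versus 53.0 kg) might be taken as the matched gap. Put in as g, it gives biases of −15 to −90 kcal/day and false-positive rates of 13% to 98%. But it is an overall between-group difference chosen for power, not a forecast at equal loss, so these figures should not be used as the size of the problem.

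**Conclusion.** The point holds for resting metabolic rate only, and conditionally. The stated basis of comparison cannot separate a fall due to less lean tissue from an adaptive fall. If the diets differ in lean loss at equal weight or fat loss, the metabolic-rate comparison is biased towards the Part 1 hypothesis; if they do not, there is no bias.

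The documents supply no slope, SD or matched lean gap. A 1 kg gap, giving about 6 to 33 kcal/day and 7% to 36% false positives, is an illustration under the assumptions listed, not an estimate for this trial.

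It would go too far to conclude that Part 1 as a whole is biased, or that Parts 1 and 2 are circular. Metabolic rate is one of many Part 1 responses, and the argument has not been shown for appetite, hormones, bone markers or activity.

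**What to change.** State in the analysis plan that the between-diet comparison of resting metabolic rate adjusts jointly for fat-free mass and fat mass at the same visit. Alternatively, fit a month-0 regression of metabolic rate on both masses in all women, and compare measured minus predicted rate at later visits between the arms as randomised.

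Report the absolute rate alongside, and rest any claim of a stronger adaptive response in metabolic rate on the adjusted comparison.

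The cost is a sentence in the plan and a few lines of code, since both masses are already measured at each Part 1 visit. The downside is slight extra noise, from the added covariate or the prediction equation. The joint model conditions on measurements taken after randomisation, which is a further reason to show the absolute rate beside it.

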## Part 2: Effects of VLED versus conventional diet on body composition

**Rationale.** While there is strong evidence that VLEDs lead to adaptations that can have deleterious effects on body composition, and limited evidence that such adaptations may be stronger during VLED than conventional diets, no long-term randomised controlled trials have directly compared the effects of VLED or conventional diet on body composition (adiposity, including central adiposity and hepatic fat content, lean body mass, muscle diameter, muscle strength and bone density). This question is of utmost clinical significance given the importance of maintaining optimum body composition for reducing the risk of diabetes, cardiovascular disease, frailty and osteoporosis, and given the increasing use of VLEDs for the clinical management of overweight and obesity.

**Parameters of body composition and metabolic health.** At 0, 3, 6, 12, 24 and 36 months after commencement of VLED or conventional diet, parameters of body composition and metabolic health will be measured as outlined in the figure above (lower box). Our established gold-standard techniques for in-depth analysis of body composition, combined with the clinical facilities and equipment available to us as well as our expertise in the analysis of such data as described below will enable us to obtain definitive answers as to the effects of VLED versus conventional diet on body composition. In addition, we will also perform non-invasive tests of vascular health at 0, 3, 6, and 36 months after commencement of either diet, using methodology established by [name], in order to assess any differences between the two diets with respect to changes in cardiovascular risk. It is necessary to measure these parameters at multiple time points; whereas the diets will likely have differential beneficial or adverse effects on body composition after 3, 6 or 12 months, a question of vital relevance to long-term structural and metabolic health is whether any such differences are sustained for up to 24 and 36 months after commencement of either diet.

Measurements are weight, waist and hip circumference, total fat mass and fat free mass calculated with the gold standard 4-compartment model using independent measures of total body density (measured by plethysmography using a BodPod®, Life Measurement Inc, Concord, CA, USA), total body water (determined by deuterium dilution), and bone mineral content (determined by dual energy X-ray absorptiometry – DXA – using a Lunar Prodigy, Madison, WI, USA) as published by [name]. In addition, abdominal adiposity will be estimated from investigation of DXA scans between lumbar vertebrae L2 and L4 and L3 and L6. As the effect of abdominal adiposity on metabolic health is determined not only by total fat content but also by fat distribution, we will use the Siemens Sonata (Malvern, PA, USA) 1.5 Tesla magnet at Royal Prince Alfred Hospital to determine total, visceral and subcutaneous adiposity by magnetic resonance imaging (MRI), and hepatic fat content by magnetic resonance spectroscopy (MRS), which correlates closely with triglyceride analysis of liver biopsies. Additionally, as evidence links thigh fat content to reduced risk of metabolic disease as recently reviewed by Associate [name], and as reduced muscle mass predicts adverse events such as impaired gait, disability and falls, MRI will also be performed on the thigh to determine thigh fat content and thigh muscle diameter. Abdominal MRI studies will be performed at the level of the L4-L5 inter-vertebral disc. Mid-thigh MRI studies will be performed at the midpoint between the patella and inguinal crease. All data will be analysed

using the SliceOmatic Version 4.2 rev-1 software package (Tomovision Inc, Montreal, QC, Canada). All MRI and MRS methodology has been previously established and published by [name]. Bone mineral density will be determined by DXA at lumbar spine and hip as published in high impact journals by Associate [name]. As [name] has shown that weight loss without strength training significantly reduces fat free mass, and as there may be differences in the effect of VLED and conventional diet on fat free mass, muscle strength will be measured by dynamometry, as previously published by Associate [name]. Moreover, a 6-minute walking test will be performed at each time point (after habituation to the test at t = -0.5 months), as a general measure of functional and cardiorespiratory fitness. Additionally, fasting serum glucose, insulin, triglycerides, cholesterol and glycosylated haemoglobin will be assessed at Royal Prince Alfred Hospital. Together with waist circumference and blood pressure measurements, these measures will be used to assess metabolic syndrome stratification. Vascular health will be assessed by 1 flow-mediated dilatation (FMD), before and after inflation of a blood pressure cuff as well as acute administration of the vasodilator glyceryl trinitrate; 2 EndoPAT; 3 measurement of carotid intima-media thickness using ultrasound; and 4 pulse wave velocity, an index of vascular stiffness.

**Data Analysis.** All data analyses will be performed using the SPSS statistical software package version 17.0 (SPSS Inc, Chicago, IL, USA). Repeated measures ANOVA will be used to compare all subjects on VLED and conventional diet with respect to changes in parameters of body composition and metabolic or vascular health. Where a significant difference between diets is detected, posthoc analyses will subsequently be used to identify the time points that differ.

**Outcomes Part 2:** This rigorously controlled study, using a suite of sensitive state-of-the-art indices of body composition, metabolic and vascular health, will show for the first time whether VLED has any effects on body composition, muscle strength, metabolic and vascular health relative to effects induced by weight loss by conventional diet. For instance, although it is expected that VLED will produce greater losses of total and central adiposity relative to conventional diet up to 12 months after commencement of the diet, is this benefit maintained throughout the 36-month follow-up period, or is there a stronger rebound regain than that seen after conventional diet? Additionally, although VLED may produce greater losses in fat free mass, muscle diameter, muscle strength and bone density at early time points relative to conventional diet, does any such difference persist until 36 months? Results from this investigation will shape the direction of clinical management of obesity by demonstrating the safety or otherwise of VLED and conventional diet with respect to body composition, an important determinant of long-term metabolic health and independent living.

**OVERALL OUTCOMES AND SIGNIFICANCE:** Unless we can develop more effective weight loss strategies for the millions of overweight or obese people in Australia, the negative impact of obesity on human lives and the national health budget in the ensuing 50 years will be intolerable. VLEDs have proven to be effective for weight loss and safe in the short term, and with their increasing clinical use it is essential to determine their long-term efficacy and safety in relation to changes in body composition that could influence subsequent development of metabolic diseases and structural diseases such as sarcopenia and osteoporosis. Our team is well placed to deliver the outcomes of this research. With over 25 years of hospital-funded clinical experience in helping people to lose weight by VLEDs and lifestyle intervention, our expertise in

integrated assessment of energy homeostasis and appetite and our state-of-the-art methodologies for measurement of body composition and metabolism, we are in a highly competitive position to be able to fully explore the promising potential of VLEDs as an effective anti-obesity treatment.

